## Abstract

**Background:**

Pain management is a critical component of comprehensive postsurgical care, as it influences patient safety and outcomes, and inadequate control has been associated with the development of chronic pain syndromes. Despite recent improvements, the management of postoperative pain following total knee arthroplasty (TKA) remains a challenge. The use of opioid-sparing, multimodal analgesic regimens has broad support, but there is a paucity of high-quality evidence regarding optimal postoperative protocols and novel approaches are needed. Dextromethorphan stands out among both well-studied and emerging pharmacological adjuncts for postoperative pain due its robust safety profile and unique pharmacology. The purpose of this study is to evaluate the efficacy of multi-dose dextromethorphan for postoperative pain control following TKA.

**Methods:**

This is a single-center, multi-dose, randomized, double-blinded, placebo-controlled trial. A total of 160 participants will be randomized 1:1 to receive either 60 mg oral dextromethorphan hydrobromide preoperatively, as well as 30 mg 8 h and 16 h postoperatively, or matching placebo. Outcome data will be obtained at baseline, during the first 48 h, and the first two follow-up visits. The primary outcome measure will be total opioid consumption at 24 h postoperatively. Secondary outcomes related to pain, function, and quality of life will be evaluated using standard pain scales, the Knee Injury and Osteoarthritis Outcome Score for Joint Replacement (KOOS, JR) questionnaire, the Patient-Reported Outcomes Measurement Information System (PROMIS-29) questionnaire, and clinical anchors.

**Discussion:**

This study has a number of strengths including adequate power, a randomized controlled design, and an evidence-based dosing schedule. As such, it will provide the most robust evidence to date on dextromethorphan utilization for postoperative pain control following TKA. Limitations include not obtaining serum samples for pharmacokinetic analysis and the single-center study design.

**Trial registration:**

This trial has been registered on the National Institute of Health’s ClinicalTrials.gov (NCT number: NCT05278494). Registered on March 14, 2022.

**Supplementary Information:**

The online version contains supplementary material available at 10.1186/s13063-023-07240-0.

## Background

### Introduction

Postoperative pain management is a critical component of comprehensive postsurgical patient care [1]. Postoperative pain not only affects patient well-being and satisfaction, but also can lead to deleterious events that can impact operative outcomes, including tachycardia, hyperventilation, decreased alveolar ventilation, poor wound healing, and insomnia [2]. There is also evidence that poorly controlled pain after surgery may elicit pathophysiologic neural alterations, including peripheral and central sensitization that can evolve into chronic pain syndromes [1].

While there have been notable improvements in the way postoperative pain is managed in the last decade, significant challenges remain, particularly with respect to total knee arthroplasty (TKA). For example, the range of pain scores reported following TKA is greater than most other elective surgeries [3]. Historically, opioids have been the preferred drugs of choice for pain management following TKA. However, excessive opioid administration is associated with significant side effects, including ventilatory depression, sedation, nausea, vomiting, pruritus, ileus, urinary retention, and constipation [1, 4]. Additionally, increasing opioid use within the early postoperative period following TKA is associated with a dose-dependent risk of periprosthetic joint infection and venous thromboembolic events [5, 6]. Moreover, liberal opiate utilization in healthcare has directly contributed to the opioid epidemic in the USA over the past 2 decades [7, 8]. In response, arthroplasty surgeons have significantly reduced opioid prescriptions in recent years to mitigate the risk of dependence [9].

A broad consensus has emerged in support of opioid-sparing, multimodal analgesic regimens [2]. The principal goal of multimodal analgesia is to target different steps of the pain pathway, resulting in more effective pain control with fewer side effects [10]. However, while multimodal protocols have consistently demonstrated improved pain control with less reliance on opioids, there is a lack of evidence regarding optimal postoperative protocols and pathways [11, 12].

Dextromethorphan stands out among both well-studied and emerging pharmacological adjuncts for postoperative pain due its robust safety profile and unique pharmacology. Dextromethorphan was first approved by the Food and Drug Administration (FDA) in 1958 and is currently one of the most common compounds found in over-the-counter antitussives [13]. As such, there is extensive data demonstrating that adverse drug reactions tend to be infrequent, short term, and usually mild [14]. Its clinical applicability is further supported by its wide therapeutic window, lack of major contraindications, and the fact that there are no special monitoring requirements for its use [15]. With respect to its unique pharmacology, dextromethorphan is structurally related to alkaloid opioids such as morphine [15], but does not interact with the mu receptor or produce typical opioid effects, including dependence [16]. It is also known to have many interactions with several different receptor sites, including activity as a low affinity antagonist at NMDA receptors [16].

### Clinical and preclinical data

After tissue injury, pain is transmitted via A-delta and C-sensory fibers to dorsal horn neurons, leading to hyperexcitability via activation of NMDA receptors [17–19]. The resulting effect causes both peripheral sensitization, which is a reduction in the threshold of nociceptive afferents, and central sensitization, which is an activity-dependent increase in the excitability of spinal neurons [20]. This process has been described as the “wind-up” phenomenon, which produces prolonged and more severe pain [18]. Dextromethorphan is thought to mitigate these effects by blocking NMDA receptors along the spinothalamic tract, reducing the threshold for pain transmission via the A-delta and C-sensory fibers [20]. However, it is also likely that additional pathways are involved. For example, recent studies have used nerve ligation animal models to show that dextromethorphan-mediated improvements in hyperalgesia may be related to the inhibition of glucocorticoid receptor-mediated neuroinflammation [21] and decreased expression of pTyr1336NR2B receptors [22].

In addition to the aforementioned preclinical data, there is also strong evidence that dextromethorphan has beneficial effects when used to treat pain in human subjects. Most notably, numerous randomized controlled trials have shown that dextromethorphan leads to reduced postoperative pain and opioid consumption. A 2016 meta-analysis investigating perioperative dextromethorphan as an adjunct for postoperative pain identified 40 studies, of which 21 were eligible for one or more comparisons [23]. In 848 patients from 14 trials, opioid consumption favored dextromethorphan (mean difference: − 10.51 mg intravenous morphine equivalents). Additionally, pain (as measured using 10-point visual analog scale) at 1, 4–6, and > 24 h also favored dextromethorphan (Mean difference: − 1.60, − 0.89, and − 0.92, respectively).

### Study overview

While numerous studies have demonstrated that dextromethorphan is safe and effective for the treatment of postoperative pain, no large randomized controlled trials have been published to date [23]. Moreover, the data on dextromethorphan is particularly limited with respect to its use in lower extremity surgery. Furthermore, even amongst studies that have been published, there is a high degree of heterogeneity both between and among existing trials, which limits clinical application. For example, several studies to date have included interventions with drastically different pain and recovery profiles, such as hernia repair and knee arthroscopy [24, 25].

This single-center, multi-dose, randomized, controlled, double-blind superiority study aims to determine if perioperative dextromethorphan is superior to placebo for postoperative pain in patients undergoing TKA. Qualified participants will be randomized 1:1 to receive either dextromethorphan or placebo before and after surgery. We hypothesize that dextromethorphan will significantly reduce postoperative opioid consumption at 24 h compared to placebo in patients undergoing TKA. Secondary outcomes related to pain, function, and quality of life will be evaluated using standard pain scales, such as visual analog scale (VAS) or equivalent numeric rating scale (NRS) for pain with and without movement, the Knee injury and Osteoarthritis Outcome Score for Joint Replacement (KOOS, JR) questionnaire, the Patient-Reported Outcomes Measurement Information System (PROMIS-29) questionnaire, and clinical anchors.

## Methods

### Participants, interventions, and outcomes

This is a single-center, multi-dose, randomized, double-blinded, placebo-controlled trial to evaluate the efficacy of perioperative dextromethorphan compared to placebo for postoperative pain in patients undergoing TKA. All standard of care interventions related to TKA are permitted during the trial. Patients aged 18 or older planning to undergo TKA will be screened for eligibility, as outlined in figure (Fig. 1). Those who meet inclusion/exclusion criteria and decide to participate will sign an informed consent prior to randomization. Patients randomized to the treatment group (*n* = 80) will receive 60 mg oral (pill) dextromethorphan hydrobromide preoperatively, as well as 30 mg 8 and 16 h postoperatively. Patients randomized to the control group (*n* = 80) will receive analogous oral placebo at the same time points.

**Fig. 1 Fig1:**
[figure not shown]
Study design flowchart. TKA = total knee arthroplasty; AEs = adverse events; VAS = visual analog scale; KOOS JR = Knee injury and Osteoarthritis Outcome Score for Joint Replacement; PROMIS = Patient-Reported Outcomes Measurement Information System

A standardized, multimodal anesthetic protocol will be implemented. Preoperatively, patients will receive up to 400 mg celecoxib and 1000 mg acetaminophen. Intraoperative anesthetics will include spinal-epidural (15 mg bupivacaine) and propofol (75–100 µg/kg/min titrated to sedation). In the inpatient postoperative setting, oral oxycodone will be available as needed. All pain medications may be adjusted as indicated. All such adjustments will be logged and reported with the final published results.

Participants have the right to withdraw at any point during the course of the study without prejudice. Additionally, the investigator can discontinue participants at any time if medically necessary. Participants may also be withdrawn from the study for the following reasons: (1) concerns for patient safety, (2) noncompliance with study procedures or obligations, or (3) patient withdrawal of consent. In the event that a patient withdraws due to an adverse event thought to be at least possibly related to study treatment, they will be followed until the adverse event resolves or the patient is deemed medically stable by the Principal Investigator. All findings will be documented.

To ensure adherence to intervention protocols, the study drug or placebo will only be administered while the patient is hospitalized for their standard of care treatment. During this time, patients will receive extensive monitoring that is comparable to (or better than) what the standard patient receives when hospitalized for acute medical illness, including a nursing ratio that is equal to or better than 4:1. In addition, dedicated research staff and investigators will be available to ensure all interventions are administered appropriately.

The primary outcome will be the mean difference in postoperative opioid consumption (morphine equivalents) at 24 h. Secondary outcomes include mean subjective postoperative pain at 6, 12, 24, and 48 h after surgery, as measured using VAS (or equivalent NRS) with and without movement preoperatively; mean postoperative opioid consumption at 48 h; mean long-term pain and function, as measured using the pathology-specific KOOS, JR; mean overall subjective status, as measured using the 29 question PROMIS-29 questionnaire; and subjective improvement, as measured using clinical anchors for pain and overall improvement. Details regarding enrollment, interventions, assessments, visits, and when specific outcomes are obtained can be found in Table 1. In addition to efficacy outcomes, this study has several exploratory objectives, which may be reported independently from the main study results. The first of these exploratory aims is to assess whether baseline factors (e.g., poor physical function, anxiety, depression, fatigue, sleep disturbance) are associated with a differential response relationship to dextromethorphan. Second, we will plan to perform a retrospective review to assess whether dextromethorphan has an effect on the anesthetic course.

**Table 1 Tab1:** Study calendar: Screening activities may be performed any day up to and including day 1 on study, but will always be performed prior to administration of study drug or placebo. POD1 = post-op day 1; KOOS JR = Knee injury and Osteoarthritis Outcome Score for Joint Replacement; PROMIS = Patient-Reported Outcomes Measurement Information System; 1 = As clinically indicated. A symptom-directed physical exam to be completed for AEs which are at least possibly related to study treatment

**Study procedure**	**Screening** **(day − 90)**	**Day 1**				**48 ± 4 h**	**Week 6 ± 3**	**Final** **(3–6 months)**
		**Pre-op**	**8 ± 4 h**	**16 ± 4 h**	**24 ± 4 h**			
**Screening/administrative**								
Sign main informed consent form	x							
Inclusion/exclusion criteria	x							
Medical history and demographics	x							
**Study drug administration**								
Administration of study drug or placebo		x	x	x				
**Safety assessments**								
Physical examination	x	x	x^1^	x^1^	x^1^	x^1^	x	x
Vital signs	x	x	x^1^	x^1^	x^1^	x^1^	x	x
Prior therapies	x							
Physical measurements	x							
Hematology	x							
Serum chemistry	x							
**Outcome evaluations**								
Post-op opioid use					x	x	x	x
VAS-pain with movement	x		x	x	x	x	x	x
VAS-pain at rest	x		x	x	x	x	x	x
KOOS JR	x						x	x
PROMIS-29	x						x	x
Clinical anchors							x	x
Adverse events			x	x	x	x	x	x

The analysis for the primary outcomes will be by intention-to-treat (ITT). All subjects will be analyzed according to randomization status, regardless of the actual treatment received, compliance with therapy, or adherence to the study protocol. For the primary study aim, we will compare the mean difference in postoperative opioid consumption between the placebo and control groups using generalized linear models (GLM) with a Gaussian family specification, assuming the data are normally distributed. If the data are not normally distributed, we will specify a more appropriate distribution based on a visual evaluation of the data using histograms. We will also use GLM to examine the relationship between treatment and outcome at each time point at which outcomes are measured. Last, for outcomes obtained at multiple time points, we will model the effect across all time points using a multi-level mixed effects model to account for repeated measures. Confounders will be defined as variables, which, when added to the model, alter the effect estimate by > 15%. Potential a priori confounders include body mass index (BMI), sex, age, race, and American Society of Anesthesia (ASA) grade. A *p*-value of < 0.05 will be considered statistically significant.

In addition to ITT analysis, per-protocol and sensitivity analyses will also be conducted. The per-protocol analysis will include only those participants who were protocol-adherent, as defined by their having received all assigned treatments and completed all follow-up visits. The sensitivity analyses will aim to identify potential sources of bias or uncertainty using various imputation methods.

There are 2 prior studies which can be used to estimate sample size for the proposed trial. The first was published by Wadhwa et al. in 2001 [26] and the second by Entezary et al. in 2013 [27]. Entezary et al. provides data that is consistent with a more conservative approach, as they used a much lower dose and investigated dextromethorphan for postoperative pain following arthroscopy–an intervention that results in relatively less pain than TKA. Using the smaller effect size from Entezary et al. (*μ* =  − 2.4, *σ* = 5.4) and standard methodology to compare the means using the T statistic with a non-centrality parameter [28, 29], a sample size of 160 patients (80 patients per group) would give 80% power to detect a difference in postoperative opioid consumption with a two-sided Type I error rate of 0.05. In contrast, using the same methodology for the study published by Wadhwa et al. yields a standardized effect size of 0.53, which corresponds to a sample size of 112 patients (56 patients per group). Given these estimates, we plan to recruit a total of 160 patients, which can accommodate 5–10% dropout. However, it should be noted that even if 5–10% of patients are lost to follow-up, the planned recruitment remains conservative. This is because the high doses used by Wadhwa et al. may not have necessarily increased the effect size in their study. In fact, it is possible that the larger dose used by Wadhwa et al. actually negatively impacted their effect size (by increasing adverse events), but these negative effects may have been offset by the fact that TKA is markedly more painful than knee arthroscopy.

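### The primary model's distribution may be re-chosen from histograms of the trial data, so the confirmatory model, and possibly its effect measure, is settled only after the data are seen

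*Protocol article*

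**What the plan says.** All the relevant text of the protocol article is in Methods, under Participants, interventions, and outcomes.

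- Outcome definition (before Table 1): "The primary outcome will be the mean difference in postoperative opioid consumption (morphine equivalents) at 24 h".
- Primary model (after Table 1): the arms are compared "using generalized linear models (GLM) with a Gaussian family specification, assuming the data are normally distributed".
- Fallback, in the next sentence: "If the data are not normally distributed, we will specify a more appropriate distribution based on a visual evaluation of the data using histograms".
- Sample size: it uses "standard methodology to compare the means using the T statistic with a non-centrality parameter", with a difference of −2.4 and an SD of 5.4. At a two-sided alpha of 0.05, the paragraph concludes that "a sample size of 160 patients (80 patients per group) would give 80% power to detect a difference in postoperative opioid consumption".

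The fallback comes with no threshold for non-normality, no list of families and no link function. Nothing says whether the histograms pool the two arms or who looks at them. Under Assignment of interventions, blinding covers participants and the investigators who recruit and treat; the analyst is not mentioned.

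**The concern.** Outcome definition, default model and sample size all point to one quantity: a difference in mean morphine equivalents. The fallback loosens that in two ways.

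1. **Timing.** The model behind the single confirmatory p-value is open until someone has judged a plot of the outcome. Two competent analysts could reach different models from the same histogram, and nothing in the article says which is right.
2. **Effect measure.** Changing the family raises the question of the link. With a log link, the treatment coefficient is a log ratio of means. The article does not say that the mean difference is kept when the family changes.

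The fallback could plausibly be reached. Postoperative oxycodone is given as needed, so 24-h use cannot be negative and may be zero for some patients. Right skew is a reasonable expectation, but it is an assumption: the article gives no distribution, control mean or proportion of zeros.

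**Working it through.** **1. The plan's own figure.** Inputs from the sample size paragraph: difference 2.4, SD 5.4, two-sided alpha 0.05, power 80%.

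Normal approximation: n per arm = 2 × (1.960 + 0.842)² × (5.4/2.4)² = 2 × 7.85 × 5.0625 ≈ 79.5, so 80. With the noncentral t, n = 80.4 per arm, and power at 80 per arm is 79.8%. The stated 160 is reproduced, and it is a calculation for a comparison of means.

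**2. What a log link does to the planned effect.** Ratio = (control mean − 2.4) / control mean. The control means here are assumed.

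- Control mean 10: 7.6/10 = 0.76.
- Control mean 30: 27.6/30 = 0.92.

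The same planned difference gives quite different ratios, so a reported ratio cannot be set against the −2.4 without the control mean.

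**3. Type I error.** Null simulation, 80 per arm, 20,000 trials per row, assumed outcome shapes without zeros. The gamma log-link test is z = ln(m₁/m₂) / √(2φ/n), where φ = Σ((y − m)/m)² / (2n − 2). A pooled skewness above 1 stands in for the histogram look. The Monte Carlo margin near 5% is 1.96 × √(0.05 × 0.95/20,000) ≈ 0.3 percentage points.

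| Assumed shape | Fixed Gaussian | Gamma log link always | Gamma log link if skewness > 1 | Smaller p of Gaussian and gamma | Smallest p of Gaussian, gamma and log-transformed |
|---|---|---|---|---|---|
| Gamma, CV 0.71 | 5.0% | 5.4% | 5.4% | 5.4% | 7.3% |
| Gamma, CV 1.0 | 5.1% | 5.6% | 5.6% | 5.6% | 8.2% |
| Lognormal, sigma 0.8 | 4.8% | 6.0% | 6.0% | 6.0% | 8.0% |

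Other runs with assumed gamma-shaped use:

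- With 0–20% zeros: fixed Gaussian 4.9–5.2%, skewness-triggered switch to gamma log link 5.2–5.5%.
- With gamma shapes 1 to 4, 0–20% zeros and a t reference for the gamma-variance model: fixed Gaussian 4.7–5.2%, switch 4.8–5.7%, always gamma 4.8–5.7%.
- A smaller run (2,000 trials per scenario, 10–20% zeros): fixed Gaussian 3.8–4.5%, with a Monte Carlo margin of about 1 point. This gives no sign of a liberal test.

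**4. Reading the results.** The fixed Gaussian test does not exceed its nominal size beyond simulation error in any scenario. The switch column matches the always-gamma column, so the small excess comes from the gamma Wald test and not from looking at the histogram. Rates of 7–8% appear only when a log-transformed analysis is added and the smallest p-value is kept.

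**The case against.** The best defence is that a histogram shows shape, not treatment p-values, and that the rule changes a distribution within a GLM. On that reading the analyst looks once, picks a sensible family and reports it. Step 3 supports this: the cost in type I error is then at most about one percentage point.

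A reader might infer two stronger claims, and neither is supported.

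- **That the rule inflates type I error to 7% or far more.** The 7–8% figures describe a search for the most favourable p-value, which the article does not prescribe, and the log transform in that search is not a GLM family. An unscaled Poisson model rejects 39–54% of the time in the simulations of step 3. However, the article names no count model, and morphine equivalents are an amount, not a count.
- **That the primary estimand is undefined or becomes a ratio.** The outcome definition is a mean difference. A non-Gaussian family with identity link keeps it, and a log-link fit can be converted back to a difference. The ratio is a possibility left open.

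Two further objections carry weight. Candidate families, link and blinding of the look are details that an analysis plan could supply, so their absence from an article is not in itself the fault. Checking the raw outcome instead of residuals also matters little here: with two arms planned 2.4/5.4 = 0.44 SD apart, the two histograms would look nearly alike.

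What stands is the rule itself. The article states that the model is re-chosen from the data, and an analysis plan would have to override that sentence, not just complete it. The sensitivity analyses it describes concern imputation methods and do not cover the choice of distribution.

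**Conclusion.** The point holds as one of prespecification, with a small numerical consequence. The confirmatory model, and possibly the scale of the reported effect, is settled only after outcomes are seen, although the trial is defined and powered on a mean difference. Used in good faith, the rule gives a type I error of about 5.2–6.0% (4.8–5.7% where the gamma test uses a t reference), against about 5% for the fixed Gaussian model. A rate of 7–8% is what the wording fails to prevent, not what it asks for.

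The switch is not needed to protect type I error: at 80 per arm the Gaussian comparison of means holds its size under every skewed shape tried. All these rates rest on assumed gamma and lognormal distributions and on a skewness cut-off standing in for a visual judgement.

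This is a cheap improvement, not a threat to the trial's validity.

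**What to change.** - Delete the histogram sentence.
- State that the primary analysis is the difference in mean 24-h morphine equivalents from a Gaussian, identity-link model, whatever the shape of the data. Robust standard errors are optional, since the plain model already holds its size.
- Name one alternative as a prespecified sensitivity analysis, for example a Wilcoxon test with a Hodges–Lehmann estimate, or a log-link model with robust standard errors.

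The change is to wording only. The 160 patients stand, because that number was already computed for a comparison of means. The possible downside is some loss of efficiency compared with a well-chosen skewed model.

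### Secondary outcomes are tested at every time point and again in a mixed model, all at an unqualified p < 0.05, so secondary claims, pain above all, are not error-controlled; the primary test is unaffected

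*Protocol article*

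**What the plan says.** All references are to the protocol article; the analysis text follows Table 1 in Methods, Participants, interventions, and outcomes.

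- **Primary outcome.** "The primary outcome will be the mean difference in postoperative opioid consumption (morphine equivalents) at 24 h". The sample-size paragraph attaches the power, and the error rate, to this outcome only: "to detect a difference in postoperative opioid consumption with a two-sided Type I error rate of 0.05".
- **Tests by time point.** "We will also use GLM to examine the relationship between treatment and outcome at each time point at which outcomes are measured".
- **Tests across time.** In addition, "for outcomes obtained at multiple time points, we will model the effect across all time points using a multi-level mixed effects model".
- **Threshold.** The same paragraph ends with a p-"value of < 0.05 will be considered statistically significant". Nothing in that sentence confines it to the primary outcome.
- **Ranking.** Pain scores, 48 h opioid use, KOOS JR, PROMIS-29 and the clinical anchors are called secondary. The word exploratory is kept for other aims: "In addition to efficacy outcomes, this study has several exploratory objectives, which may be reported independently from the main study results".
- **Pain time points.** The outcome text lists 6, 12, 24 and 48 h. Table 1 lists 8, 16, 24 and 48 h, week 6 and the final visit, for pain at rest and pain with movement alike.

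**The concern.** Read as written, the plan lets any secondary result below 0.05, at any visit and from either model, be reported as statistically significant. The text gives no order of testing, no key pain time point and no statement that these results are supportive. The per-visit models and the mixed model use the same data. If they disagree, the reader cannot tell beforehand which one counts.

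What is at stake is the reliability of statements about pain, function and quality of life. With 8 or 12 pain tests, an isolated significant time point is not rare when the drug does nothing. Such a finding could be presented with the same standing as the primary result. The pain family is not fixed either, because the outcome text and Table 1 give different times.

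**Working it through.** **1. The plan's own figure.** Inputs from the sample-size paragraph: difference 2.4, SD 5.4, two-sided 0.05, 80 per group.
- Standardised effect: 2.4 / 5.4 = 0.444.
- Normal approximation: n per group = 2 × (1.960 + 0.842)² / 0.444² = 79.5, so 80. Power at 80 per group is 80.3%.
- Noncentral t at 80 per group: 79.8%.

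The stated 160 patients and 80% power are reproduced. They concern the primary test only, and nothing below alters them. The document states no family-wise error figure for the secondary outcomes.

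**2. Counting the pain tests.**
- Outcome text: 4 times × 2 conditions (with and without movement) = 8.
- Table 1: 6 postoperative times × 2 conditions = 12.

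**3. Independent tests (correlation 0).** Chance of at least one false positive among k tests:
- either direction: 1 − 0.95^k
- in favour of the drug only: 1 − 0.975^k

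For k = 8: 1 − 0.95^8 = 33.7% and 1 − 0.975^8 = 18.3%. For k = 12: 46.0% and 26.2%.

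**4. Correlated tests.** Repeated pain scores in the same patients are correlated, so independence gives the upper end. Take k test statistics with a common correlation ρ and a shared normal factor U with density φ. For the favourable direction:

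P = 1 − ∫ [Φ((1.96 − √ρ·u) / √(1 − ρ))]^k φ(u) du

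For either direction, the bracket is replaced by the probability of falling between −1.96 and 1.96 given u. The document gives no correlations, so ρ is assumed and shown as a range.

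| Pain tests | ρ | In favour of drug (nominal 2.5%) | Either direction (nominal 5%) |
|---|---|---|---|
| 8 | 0 | 18.3% | 33.7% |
| 8 | 0.5 | 12.5% | 25.0% |
| 8 | 0.8 | 7.9% | 15.7% |
| 12 | 0 | 26.2% | 46.0% |
| 12 | 0.5 | 16.0% | 31.9% |
| 12 | 0.8 | 9.3% | 18.6% |

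**5. Adding the mixed model.** The table leaves out the across-time tests. A simulation of 400,000 draws added one across-time test per pain condition, using the equal-weight mean of the time points in place of the mixed model. Correlations between times and between conditions ranged from 0 to 0.8. It gave about 9–28% in favour of the drug and 17–48% in either direction. The mixed model therefore adds little to the error rate. What it adds is the uncertainty over which analysis decides.

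**The case against.** The strongest reply has four parts.

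**The ranking is already stated.** There is one primary outcome with its own error rate and power, and the rest is labelled secondary. This stands: the primary test is untouched.

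**Multiplicity rules belong in an analysis plan that is not shown.** Silence would be no finding. But the article is not silent. It fixes a per-visit model, a mixed model on the same data and an unqualified threshold. If an analysis plan sets a different rule, the article's sentence conflicts with it and needs aligning.

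**The plan never says that one significant time point suffices for a claim.** This is correct, and the two kinds of model can answer different questions. The rates above therefore describe what the stated threshold permits, not a decision rule that the plan adopts.

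**The trial's aim is opioid use, not pain scores.** A reader might infer that the main aim rests wholly on uncontrolled tests, because the Study overview says that the study "aims to determine if perioperative dextromethorphan is superior to placebo for postoperative pain in patients undergoing TKA". The documents do not support that. The same paragraph states the hypothesis as lower opioid consumption at 24 h and lists pain scales as secondary, and the analysis text names opioid consumption as the primary study aim. This part of the objection stands in full.

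**Conclusion.** The point holds, confined to secondary claims. For VAS pain, the chance of at least one false significant result in favour of the drug is about 8–26%, roughly three to ten times the nominal 2.5%. In either direction it is about 16–46% against 5%. Both ranges rest on assumed equal correlations of 0 to 0.8 and on 8 or 12 tests. The upper ends need independent tests, which is implausible for repeated scores in the same patients.

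A reader might go further and put the chance of a false claim of pain benefit at 25–47%. That does not hold, for two reasons:
- Both figures count results in either direction, and a result against the drug cannot support a claim of benefit.
- The 47% (at correlation 0.5) comes from 25 tests counted across Table 1 and the list of three anchors. Of these, 13 are not VAS pain: 3 opioid, 2 KOOS JR, 2 PROMIS-29 and 6 anchor tests. That count also goes beyond the outcome text, which names pain at four times, opioid use at 48 h and two anchors.

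This is a cheap improvement. It is not a defect in the primary analysis.

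**What to change.** In the statistical paragraph after Table 1:

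1. Limit the p < 0.05 significance statement to the primary intention-to-treat test of 24 h opioid consumption.
2. Make the mixed model the single analysis of each repeated secondary outcome, and estimate per-visit differences from it in place of the separate per-visit models.
3. Report secondary outcomes with 95% confidence intervals and call them supportive.
4. If a confirmatory pain claim is wanted, name one pain contrast in advance and test it at two-sided 0.05 only if the primary test is significant.
5. Reconcile the pain time points in the outcome text (6, 12, 24, 48 h) with Table 1 (8, 16, 24, 48 h, week 6, final), so that the set of tests is fixed.

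The cost is a few sentences, written before unblinding. The primary test keeps its full 0.05, 160 patients remain the target, and no data or procedures are added. The small downside is that isolated secondary results below 0.05 can no longer be called statistically significant.
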